**Discussion:**

This trial will address a critical evidence gap and may inform future guidelines regarding catheter management in CAUTI. If replacement is found to have no benefit, this could reduce unnecessary interventions, lower healthcare costs and material use, contribute to sustainability, and lessen the burden on both patients and healthcare organizations.

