### Outcome measures

The primary outcome is a recurrent CAUTI within 90 days after completion of antibiotic treatment, defined according to the same IDSA-based clinical and microbiological criteria used for inclusion. The pathogen does not have to be identical to the causative pathogen that was identified during the first episode.

All participants are instructed to contact the central study team should they experience CAUTI symptoms. Additionally, the physicians at the participating centres and general practitioners are instructed to report potential recurrences among participants.

Secondary outcomes:

Patient-related outcomes: 30-day mortality, health-related quality of life assessed using the PROMIS and EQ-5D-5L questionnaires.Process-related outcomes: time to resolution of CAUTI symptoms, time to resolution of fever, complications of catheter replacement and severity of the complications (5-level Likert scale).Resource-related outcomes: length of hospital stay, ICU-admission during hospital stay, healthcare and societal cost using a selection of items relevant for this population of the medical consumption (iMCQ) and productivity (iPCQ) questionnaire.

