### Statistical analysis

#### Sample size

It is planned to recruit 300 participants (150 in each treatment arm). For both groups, we assume a recurrence rate of 10% [18] within 90 days after start of antibiotic therapy. Analyzing the data as a non-inferiority study, taking a non-inferiority margin of 10%, and a (one-sided) type-I error rate (alpha) of 2.5%, a study with 300 participants would have a power of approximately 80%. A power of 80% would indicate that the likelihood is 80% that the upper-limit of the 95% confidence interval for the 90-day risk difference will exclude a difference of 10% in favour of the control (replacement) group. To account for post-randomization exclusions, we plan to randomize 400 participants.

An interim analysis of the overall recurrence rate will be performed after 50% of the initially planned sample size has completed 90 days of follow-up. The interim analysis will not assess treatment effectiveness, and no early stopping for efficacy or futility is planned. The sole purpose of this interim analysis is to evaluate whether the observed overall recurrence rate aligns with the assumptions used for the sample size calculation. If the recurrence rate is found to be below 7.5%, the project group will consider whether an increase in the sample size is warranted.

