### Implications and future directions

Current national and international guidelines, advice to change the catheter with a low level of evidence [1, 7, 8]. If this trial demonstrate that catheter retention is non-inferior to replacement, clinical practice could be standardized accordingly in future guideline updates. This may reduce the number of invasive procedures, decrease healthcare costs, lower material waste and alleviate patient burden without compromising safety. Conversely, if catheter retention is not found to be non-inferior, the results will strengthen the evidence base supporting current recommendations for catheter replacement and may improve adherence in clinical practice.

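### The safety statement is conditional on a recurrence-only non-inferiority result, while ICU admission is assigned to the per-protocol population alone

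*Protocol article*

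**What the plan says.** - **Protocol article, Implications and future directions.** If retention is shown to be non-inferior, practice could be standardised on it in guideline updates. The next sentence says this may reduce invasive procedures, "decrease healthcare costs, lower material waste and alleviate patient burden without compromising safety".
- **Sample size.** Only one decision criterion is given, in these words: "upper-limit of the 95% confidence interval for the 90-day risk difference will exclude a difference of 10% in favour of the control (replacement) group". The Abstract likewise ties the 10% margin to recurrent CAUTI, and Strengths and limitations claims sufficient power for that outcome only.
- **Outcome measures.** Death is a secondary outcome: "Patient-related outcomes: 30-day mortality, health-related quality of life assessed using the PROMIS and EQ-5D-5L questionnaires". ICU admission is also secondary and is grouped with length of stay and costs as resource-related.
- **Analyses of outcome measures.** The primary outcome is analysed in both the intention-to-treat and per-protocol populations. Process and resource outcomes are assigned to the per-protocol population, with no intention-to-treat counterpart mentioned. No analysis population is named for 30-day mortality.
- **Background.** CAUTI is described as able to lead to serious and sometimes fatal complications, including urosepsis. Source control is given as the theoretical rationale for replacement.

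**The concern.** The safety wording depends on a result that carries no direct information on the harms that matter most. Retention could meet the recurrence criterion whatever the trial shows on death or ICU admission. At most, a death might enter indirectly as a missing recurrence status, and not as a harm in its own right.

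The evidence that could support a safety statement is also weakened by the analysis set. ICU admission is the nearest thing in the outcome list to a marker of severe deterioration, yet it is to be compared only among patients who kept to their allocated strategy. In an unblinded trial, a patient allocated to retention who becomes severely ill may well have the catheter changed. If that counts as a deviation, the patient and the ICU admission leave the comparison together. The exclusion then depends on the course of the illness, and randomisation no longer protects the result.

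At stake is a guideline message that retention is safe. It would rest on a test of a different outcome and on an ICU comparison that may be selectively depleted.

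**Working it through.** **1. Inputs.** From Sample size: "It is planned to recruit 300 participants (150 in each treatment arm"), "For both groups, we assume a recurrence rate of 10"%, and "taking a non-inferiority margin of 10%, and a (one-sided) type-I error rate (alpha) of 2.5"%, with power of about 80%. The article also states: "To account for post-randomization exclusions, we plan to randomize 400 participants", which is about 200 per arm at 1:1 allocation. It gives no expected rate for 30-day mortality or ICU admission, so control mortality below is an assumption shown over a range.

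**2. The plan's own figure.** With 10% in both arms and 150 per arm, SE = √(2 × 0.1 × 0.9 / 150) = 0.0346. Power = Φ(0.10 / 0.0346 − 1.96) = Φ(0.927) = 82.3%. Exact enumeration over two binomials gives 81.9% with the Wald interval and 80.3% with the Newcombe interval. Farrington-Manning gives 78.8%. The stated 80% for recurrence reproduces and is not in dispute.

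**3. What the sample can say about death.** The check is the power to detect a doubling from p to 2p in the direction of harm, at two-sided 5%. By the normal approximation,

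Power = Φ{ [p√n − 1.96 √(2 p̄(1 − p̄))] / √(p(1 − p) + 2p(1 − 2p)) }, with p̄ = 1.5p.

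For p = 5% and n = 150: (0.612 − 0.730) / 0.371 = −0.317, so power is 37.6%. Exact enumeration of the pooled z test gives 36.9%.

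| Assumed control → retention mortality | 150 per arm, exact | 150 per arm, normal | 200 per arm, normal |
|---|---|---|---|
| 2% → 4% | 15% | 17% | 22% |
| 3% → 6% | 23% | 24% | 30% |
| 5% → 10% | 37% | 38% | 48% |
| 7% → 14% | 51% | 51% | 63% |
| 10% → 20% | 69% | 68% | 80% |

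By the normal approximation, power reaches 50% at a control rate of about 6.9% with 150 per arm and about 5.3% with 200 per arm. Fisher's exact test is more conservative: at 150 per arm it gives 9%, 30%, 51% and 63% at control rates of 2%, 5%, 8% and 10%.

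**4. What equal observed mortality would leave open.** Take 8 deaths of 150 in each arm (5.3%). The Wilson 95% limits for one arm are 2.7% and 10.2%. The Newcombe upper limit for the difference is √[(10.17 − 5.33)² + (5.33 − 2.73)²] = 5.5 points. An observed difference of zero would thus still be compatible with roughly a doubling, from 5.3% to 10.8%.

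**5. Analysis set for ICU admission.** No arithmetic is possible, because the article gives neither an ICU rate nor a deviation rate. The chain comes from the text: Outcome measures makes ICU admission a resource outcome, and Analyses of outcome measures puts resource outcomes in the per-protocol population. A change of catheter in the retention arm is departure from the allocated strategy. If it is prompted by deterioration, the per-protocol set loses severe cases from that arm. Losses could also occur in the replacement arm, for example if a patient is too ill for replacement within 3 days. The net direction therefore cannot be fixed in advance. The comparison is open to selection by the very outcome it measures.

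**The case against.** The strongest reply is that this is one hedged sentence in a Discussion. It says may and could, sets no rule for declaring safety, and nowhere says that a non-significant difference will be read as evidence of safety. The article claims power only for recurrence. It prespecifies mortality, ICU admission and replacement complications as outcomes, so they will be reported. All of that is correct, and it limits how much weight the wording can bear.

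Three stronger readings are tempting, and the documents do not support them.

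- **A reader might infer that the trial would miss a doubling of mortality more often than not.** That needs a baseline rate the article does not give. By the pooled test it holds only below about 7% control mortality at 150 per arm, or about 5% at 200. At 10% a doubling is more likely detected than missed. Excluding patients with a life expectancy under 90 days makes a low rate plausible but does not establish it.
- **A reader might fault the absence of a margin or bound for death and ICU admission.** Secondary outcomes commonly carry none, and a condensed article may leave such criteria to the full protocol or SAP, which are not shown.
- **A reader might object to the Abstract's phrase "If replacement is found to have no benefit, this could reduce unnecessary interventions", or to the 10-point margin allowing smaller excesses.** The first is shorthand beside a Methods paragraph that states the margin exactly. The second is what a margin means, and stakeholders considered its acceptability.

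What stands is narrower. The inference from recurrence to safety is in the article as written, and so is the assignment of ICU admission to the per-protocol population.

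**Conclusion.** The point holds in a limited form. The article links a statement about safety to a non-inferiority result defined on recurrent CAUTI alone, and it places ICU admission in an analysis set from which deteriorating patients may be removed. The first is an overstatement in wording. The second is a correctable analysis choice.

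The size of the mortality part is conditional on an assumed control rate: power for a doubling runs from about 15% (at 2%) to 69% (at 10%) with 150 per arm, and 8 v 8 deaths leaves up to about +5.5 points open. The ICU part assumes that a catheter change prompted by deterioration counts as a protocol deviation. The article does not define the per-protocol population, so that remains possible rather than certain. Neither part affects the primary analysis or its sample size, which reproduces.

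**What to change.** 1. In Analyses of outcome measures, state that 30-day mortality and ICU admission will be estimated as risk differences with 95% confidence intervals in the intention-to-treat population, with the per-protocol analysis as a supplement.
2. In Implications and future directions, limit the conclusion from the primary rule to what it shows: that an excess of recurrent CAUTI of 10 percentage points or more with retention is excluded.
3. In the same place, make any statement on safety conditional on the upper limits of the two intervals in item 1, that is, on the largest excess not excluded. A non-significant difference should not serve as evidence of safety.

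The cost is some wording and two risk differences from outcomes already being collected, with no added patients or procedures. The safety claim will be more modest, because the mortality interval may be wide. It is best settled before results are known.

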The REPLACE study aims to generate evidence to inform future recommendations for urinary catheter management in the treatment of CAUTI. We hypothesize that not changing the catheter during a CAUTI is non-inferior to replacing it with regard to the risk of recurrent CAUTI. This study therefore potentially contributes to reducing healthcare costs and sustainability by minimizing waste generated from catheter replacements, while also alleviating the workload on personnel when the procedure is redundant.

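### The Discussion reads any failure to show non-inferiority as support for replacement, although under the protocol's own assumptions most such failures would be inconclusive

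*Protocol article*

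**What the plan says.** The hypothesis, at the end of the Background, is that "not changing the catheter during a CAUTI is non-inferior to replacing it with regard to the risk of recurrent CAUTI". The article states no superiority hypothesis for replacement.

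The Sample size section states "For both groups, we assume a recurrence rate of 10" per cent, "taking a non-inferiority margin of 10%, and a (one-sided) type-I error rate (alpha) of 2.5" per cent, and that "a study with 300 participants would have a power of approximately 80" per cent. It describes success as the case in which "the upper-limit of the 95% confidence interval for the 90-day risk difference will exclude a difference of 10" percentage points in favour of replacement. The 300 are split 150 per arm. The article adds: "To account for post-randomization exclusions, we plan to randomize 400 participants".

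Analyses of outcome measures plans the risk difference with a two-sided 95% confidence interval, in both the intention-to-treat and the per-protocol population.

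Implications and future directions then says what each result would mean for practice. If non-inferiority is shown, practice could be standardised on retention. In the opposite case, "if catheter retention is not found to be non-inferior, the results will strengthen the evidence base supporting current recommendations for catheter replacement", and the article expects that adherence may improve as well.

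**The concern.** A non-inferiority test that does not reject leaves two very different situations open. Either the data show that replacement lowers recurrence, or the interval is too wide to say. The first needs a lower limit above 0 for retention minus replacement. The stated criterion looks only at the upper limit, so failing it cannot establish the first situation. The sentence nevertheless treats both alike, and says that the results *will* support the current recommendation.

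This matters because the sentence is addressed to guideline updates. The authors' own case for the trial is that current guidance rests on limited and conflicting evidence. Announcing in advance that an inconclusive trial supports the same guidance would add to that problem. The trial is also unblinded, and the article acknowledges pre-existing preferences about catheter management, so the interpretation is best fixed before results are known.

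**Working it through.** **Inputs** (Sample size section): 10% recurrence in both arms, margin 10 points, one-sided alpha 2.5% (two-sided 95% interval), 150 per arm.

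**Step 1: reproduce the stated power.** The standard error of the difference is √(2 × 0.10 × 0.90 / 150) = √0.0012 = 0.03464. Power = Φ(0.10/0.03464 − 1.96) = Φ(0.927) = 82.3%. Exact binomial enumeration gives 81.9% with the Wald interval and 80.3% with the Newcombe interval. The stated figure of about 80% is reproduced.

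**Step 2: where failure starts and where evidence for replacement starts.** By normal approximation, with 1.96 × 0.03464 = 0.0679:
- non-inferiority fails once the observed difference reaches 0.10 − 0.0679 = 3.2 points;
- the lower limit passes 0 only at 6.8 points.

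Observed differences between 3.2 and 6.8 points miss non-inferiority without showing that replacement is better.

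**Step 3: split the outcomes.** Exact enumeration, 150 per arm, replacement rate 10%, Wald interval:

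| True rate with retention | Non-inferiority missed | of which lower limit > 0 | of which interval covers 0 and 10 points | Inconclusive share of failures |
|---|---|---|---|---|
| 10% | 18.1% | 2.6% | 15.5% | 86% |
| 15% | 73.7% | 26.1% | 47.6% | 65% |
| 20% | 97.3% | 69.4% | 27.9% | 29% |

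The middle columns are percentages of all trials. With the Newcombe interval the first row becomes 19.7% missed, 2.2% with lower limit above 0 and 17.5% inconclusive, a share of 89%. The shares in the other two rows become 67% and 30%.

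**Step 4: an example.** Take 15/150 recurrences with replacement.
- 19/150 with retention: difference 2.7 points, SE = √(0.1267 × 0.8733/150 + 0.10 × 0.90/150) = 0.0366, upper limit 2.7 + 7.2 = 9.8 points (from unrounded values). Non-inferior.
- 20/150: difference 3.3 points, 95% interval −3.9 to 10.6. Non-inferiority fails, yet retention could be better by almost 4 points.
- 26/150: interval −0.4 to 15.1. Still includes 0.
- 27/150: interval 0.2 to 15.8. The first count at which the lower limit is above 0.

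On these figures, counts from 20 to 26 would all be read as supporting replacement while being compatible with no difference.

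**Step 5: sensitivity.** At equal rates of 7.5% and 150 per arm, 74% (Wald) to 81% (Newcombe) of failures are inconclusive. If all 400 randomised were analysable (200 per arm, 10% rates), 9% to 10% of trials would fail and 70% to 75% of those would be inconclusive. At 200 per arm and 7.5% the share is 44% to 48%, so inconclusive failures are no longer the majority there. That case lies outside the planned scenario.

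**The case against.** The strongest reply is that this is forward-looking comment in a Discussion, not a decision rule. The operative criterion is in the Sample size section and the analysis is in the Statistical analysis section; neither equates failure with support for replacement. The planned two-sided interval will show the lower limit to any reader. This stands, and it limits the severity. A reader might infer that the trial's test or sample size is faulty, or that the final report is bound to present an inconclusive interval as support. The documents do not support either: the sentence alters no analysis, and one Discussion sentence does not settle a future report.

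A second reply is that strengthening an evidence base claims less than superiority. At the planned rates a failure does come with an estimate leaning towards replacement, from about 3.2 points. Failure is also about five times as likely if retention is truly 10 points worse as under equality (97.3% / 18.1% = 5.4). So a failure carries some evidence in that direction. What does not stand is the unconditional *will* for a result whose interval includes 0.

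A third reply is that the 86% assumes exact equality. That is correct. A reader might take it as a property of all failures; the table shows that it is not.

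Finally, a detailed interpretation scheme may be in an analysis plan that is not shown. That would answer an omission. Here a sentence is stated wrongly, and a correct plan would contradict it.

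**Conclusion.** The point holds as an error of interpretation, at should-fix level. Failure to show non-inferiority is not, by itself, evidence for replacement, and the article says without condition that it is.

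Under the protocol's own assumptions, about one trial in five would fail with identical strategies, and 86% to 89% of those failures would leave both 0 and 10 points inside the interval. The share is lower if retention is truly worse: about 65% at 5 points and 29% at 10 points (Wald).

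The figures rest on 150 analysed per arm, a 10% replacement rate, Wald or Newcombe intervals, and a single analysis population. If both planned populations had to pass, failures under equality could only be as frequent or more frequent.

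**What to change.** Replace the sentence with a reading based on the two-sided 95% interval for retention minus replacement:

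- upper limit below 10 points: retention is non-inferior;
- lower limit above 0: evidence that replacement reduces recurrence (if the upper limit is also below 10 points, report both statements);
- interval including both 0 and 10 points: inconclusive, and not to be presented as support for replacement.

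State that the rule is read in both the intention-to-treat and the per-protocol population, and that a conclusion is drawn only where the two agree.

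The cost is wording only, since the interval is already planned in both populations. The downside is that the investigators must accept a possible inconclusive result.

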## Data Availability

No datasets were generated or analysed during the current study.

## Abbreviations

Castor EDC: Castor Electronic Data Capture (EDC)
CAUTI: Catheter-associated urinary tract infection
CFU: Colony-forming units
EQ-5D-5L: The 5-level EQ-5D version introduced by the EuroQol Group
EUCAST: European Committee on Antimicrobial Susceptibility Testing
ICU: Intensive care unit
IDSA: Infectious Diseases Society of America
iMCQ: The iMTA Medical Consumption Questionnaire
iPCQ: The iMTA Productivity Cost Questionnaire
LUMC: Leiden University Medical Centre
PROMIS: Patient-Reported Outcomes Measurement Information System
RCT: Randomized controlled trial
UTI: Urinary tract infection
